### Relevant concomitant care permitted or prohibited during the trial

Participants will not be permitted to (1) engage in any other formal weight loss or exercise programs or clinical trials during the intervention, (2) use prescription or over-the-counter anti-obesity medications or supplements, and/or (3) undergo obesity treatment with bariatric surgery.

### Statistical analysis

Using SPSS version 23 (SPSS Inc., Chicago, IL, USA), parametric and non-parametric statistical tests will be applied for data analysis. Summary statistics of each group will be computed and presented as mean, standard deviation, and proportion. Distributions of continuous variables will be tested for normality using the Kolmogorov-Smirnov test. The non-parametric Mann-Whitney *U* test will be used for asymmetrical continuous variables. Using the paired *t*-test, the baseline and end of study characteristics, as well as the laboratory results of the groups, will be compared and a *P* value of <0.05 will be considered significant. The independent sample *t*-tests will be used (or suitable non-parametric test depending on data distribution) for the between-group differences and generalized linear mixed effects models for the analysis of longitudinal data.

Results will be presented as per-protocol and intention-to-treat analysis groups. The analysis will be carried out using the intention-to-treat (ITT) principle where patients’ data will be analyzed as members of the group they were randomized to, irrespective of their compliance with the treatment as specified in the protocol. A per-protocol (PP) analysis will be carried out including all patients who strictly adhere to the protocol in terms of following the treatment, availability of measurements, and absence of major protocol deviations. ITT analysis will use a generalized linear mixed model which can inherently deal with data missing at random. An effort will be made to reduce missing data to a minimum.

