### Objectives and hypothesis

Hypothesis:Primary—prescribing a reduced caloric meal replacement at dinner will have beneficial effects on weight loss of night shift workers with obesity.Secondary—associated metabolic parameters (lipid profile, glycemic outcomes, and blood pressure) will be improved in the treatment group in comparison to the control group.

Objectives:Primary—to investigate if dinner meal replacement with a low-calorie meal replacement shake is an effective strategy to achieve a minimum 5% body weight loss in shift workers with obesity compared to conventional dinnerSecondary—to evaluate the effects on anthropometric parameters, serum lipids, glycemic outcomes, and blood pressure

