#### Interventions

The test group will be provided with a 200-kcal meal replacement shake consisting of 20.0 g of protein, 4.5 g of fat, 18.2 g of carbohydrate, and 3.6 g of fiber with other vitamins and minerals. The ingredients and the nutritional composition of the product are presented in Additional file 2. The meal replacement will be donated by a pharmaceutical manufacturing company (Astron Limited). However, the manufacturer/sponsor organization will not be involved in any aspects related to the conduct of the study, including patient recruitment, follow-up, and analysis of data.

The meal replacement product will be in powdered form, and participants will be instructed to prepare the liquid shake by mixing 53 g of powdered meal replacement with 400 mL of water. They will be asked to consume one serving of the meal replacement shake to replace dinner for 5 days of the week for a period of 8 weeks. The intervention group will be given sufficient meal replacement tins with a label indicating the ingredients and the preparation method. Participants will be instructed not to consume any additional food between dinner in the evening, and breakfast the following morning. The breakfast and lunch meals will be recommended as normal meals (the meals that they habitually eat).

The control group will be asked to continue their usual dinner meals during the study period. In addition, both the groups will be given general dietary and lifestyle advice through the distribution of leaflets which includes basic dietary advice according to Sri Lankan food-based dietary guidelines. Both groups will be advised to continue their habitual physical activities.

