### Primary outcome

The primary outcome will be the proportion of participants that had a 5% body weight loss from baseline.

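### For the continuous outcomes the plan lists within-arm paired tests, unadjusted between-arm tests and a mixed model without saying which decides; the paired tests cannot answer the between-arm hypothesis

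*Protocol article*

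**What the plan says.** The protocol's Objectives and hypothesis section states the secondary hypothesis as a comparison between arms: lipids, glycemic outcomes and blood pressure "will be improved in the treatment group in comparison to the control group". The Secondary outcomes section lists 12 continuous measures, all worded as changes.

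The Statistical analysis section then names several methods for continuous data:

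- Paired t-tests, by which "the baseline and end of study characteristics, as well as the laboratory results of the groups, will be compared". The same sentence adds that a P "value of <0.05 will be considered significant". This is the only p-value threshold in that section.
- Independent-sample t-tests, or a non-parametric alternative, "for the between-group differences and generalized linear mixed effects models for the analysis of longitudinal data". No baseline covariate is mentioned, and the text does not say whether the tested variable is the week-8 value or the change.
- A mixed model a second time, in the next paragraph: "ITT analysis will use a generalized linear mixed model which can inherently deal with data missing at random".

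No sentence says which of these carries the conclusion for a given outcome. Under Interventions, "both the groups will be given general dietary and lifestyle advice".

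**The concern.** A paired test within the intervention arm asks whether that arm changed. The hypothesis asks whether it changed more than the control arm. The two questions separate whenever both arms move together. That is plausible here, because both arms receive advice leaflets and both are measured repeatedly. Significance in one arm and not in the other is not evidence of a difference between them.

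The outcome structure makes this practical. Only anthropometric measures are taken at week 4. Of the 12 listed secondary outcomes, that covers waist and hip circumference. The other ten (body fat, fat-free mass, two blood pressures, four lipids, fasting glucose, HbA1c) have baseline and week 8 only, which is the layout that the paired sentence describes, and that sentence names the laboratory results. Twelve outcomes in two arms allow 24 such tests.

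A second, smaller matter is precision. Every outcome has a baseline value, and a trial of 44 gains from using it as well as possible.

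**Working it through.** **Evaluable number.** The plan's own formula, with 0.10 against 0.50, two-sided 5% and 80% power, gives (0.1×0.9 + 0.5×0.5) × ((1.960 + 0.842)/0.4)² = 16.68, so 17 per arm. With 20% dropout, 17/0.8 = 21.25, so 22 per arm. The plan's figures reproduce, and 17 per arm is used below.

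**Within-arm tests when the arms do not differ.** The plan gives no expected change or SD for these outcomes, so the common true change d, in units of the SD of the change, is assumed over 0 to 1.0. The paired t-test in one arm has noncentrality d√n on n−1 degrees of freedom. At d = 0.5 and n = 17 this is 0.5 × √17 = 2.06, and the power is p = 0.491. The arms are independent, so the chance that only the intervention arm is significant is p(1−p) = 0.491 × 0.509 = 0.25.

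| Common change d | Intervention arm significant | Intervention arm only |
|---|---|---|
| 0 | 5% | 5% |
| 0.3 | 21% | 17% |
| 0.5 | 49% | 25% |
| 0.7 | 77% | 18% |
| 1.0 | 97% | 3% |

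A simulation of 40,000 trials at d = 0.5 gave 49.1% and 24.8%. The between-arm t-test rejected in 5.1%, as it should. With all 22 per arm the figures at d = 0.5 are 61% and 24%.

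**Precision of the between-arm comparison.** Let r be the correlation between baseline and week 8, with equal SDs at both times. The plan gives no r, so a range is shown. In units of the variance of the final-value comparison, a t-test on change has 2(1−r) and ANCOVA has 1−r². ANCOVA relative to change is therefore (1−r²)/(2(1−r)) = (1+r)/2.

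| r | ANCOVA / change-score t-test | ANCOVA / final-value t-test |
|---|---|---|
| 0.3 | 0.65 | 0.91 |
| 0.5 | 0.75 | 0.75 |
| 0.7 | 0.85 | 0.51 |
| 0.8 | 0.90 | 0.36 |
| 0.9 | 0.95 | 0.19 |

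Example with 17 per arm, a true difference of 0.5 SD of the outcome and r = 0.7: power is 29% on final values, 45% on change and 51% with ANCOVA.

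**The case against.** The strongest reply is that the plan does contain a between-arm analysis. It assigns separate tests to the group difference and names a mixed model twice, once as the intention-to-treat analysis. The Sample size section sets the 5% level for the comparison of arms, so P<0.05 can be read as a general level and not one reserved for paired tests. Nowhere does the text say that a significant within-arm change will be taken as efficacy.

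Much of this stands, and it rules out several stronger readings:

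- *The paired tests and unadjusted t-tests are the whole plan.* They are not; the mixed model is there too. Its terms are not given, which an article may leave to the analysis plan.
- *The baseline values are wasted.* The secondary outcomes are defined as changes, and a t-test on change uses baseline and is valid in a randomized trial. The large savings in the last column of the second table apply only if final values are tested, which the text does not say.
- *False claims become likely.* The chance that exactly one arm is significant reaches 50% at d = 0.5, but half of those trials favor the control arm. The misleading pattern is the 25%, and it misleads only if the paired result is reported as the finding.
- *The primary result is at risk.* "The primary outcome will be the proportion of participants that had a 5% body weight loss from baseline" is a binary outcome, and none of these t-tests applies to it.
- *The normality pre-test is a defect of the same weight.* The plan says "Distributions of continuous variables will be tested for normality using the Kolmogorov-Smirnov test". How often that test misses skewness depends on an assumed distribution and on which version is run, and no effect on a conclusion can be shown from the document.

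What the reply does not remove is that a p-value rule is attached to a test that cannot address the stated hypothesis, and that no analysis is named as decisive.

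**Conclusion.** The point holds for the continuous outcomes. The within-arm paired tests do not test the secondary hypothesis. With no difference between arms and 17 per arm, they would show a significant change in the intervention arm in 5% to 97% of trials, and in that arm only in 3% to 25%, for a common change of 0 to 1.0 SD. A between-arm test stays at 5% throughout. These figures rest on assumed changes.

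The missing baseline adjustment is a matter of efficiency and not an error. Against a change-score t-test, ANCOVA lowers the variance by 5% to 15% for r of 0.9 to 0.7, and by up to 35% at r = 0.3. The saving is larger only for high r with final values tested. The correlations are assumed.

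The improvement to a stated method is worth making before the analysis. It does not touch the primary outcome or the sample size.

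**What to change.** In the Statistical analysis section:

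1. Report within-arm changes as mean (SD) for each arm, without p values, and remove the paired t-tests as significance tests.
2. Name one between-arm analysis as inferential for each continuous outcome, and give the adjusted difference with a 95% confidence interval. For outcomes measured at baseline and week 8 only, regress the week-8 value on arm and baseline. For those also measured at week 4, use the planned mixed model with the baseline value included.
3. Attach the 5% level to that between-arm estimate. If the unadjusted t-test or Mann-Whitney test is kept, label it supportive.

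The cost is a few reworded sentences. The measurements, the software and the 44 participants stay as planned, and the article states that enrollment had not begun.

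### Paired t-tests within each arm are planned as significance tests for secondary outcomes, although the secondary hypothesis is shake against control and the text does not say which test decides

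*Protocol article*

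**What the plan says.** Under Objectives and hypothesis, the protocol article frames the secondary hypothesis between arms: lipids, glycaemic measures and blood pressure "will be improved in the treatment group in comparison to the control group".

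The Statistical analysis section then plans three kinds of analysis for continuous outcomes:

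- Paired t-tests, by which "the baseline and end of study characteristics, as well as the laboratory results of the groups, will be compared". The same sentence ends with the rule that a P "value of <0.05 will be considered significant". No other significance threshold appears in that section.
- In the next sentence, independent-sample t-tests ("or suitable non-parametric test depending on data distribution) for the between-group differences"), together with "generalized linear mixed effects models for the analysis of longitudinal data".
- In the following paragraph, the intention-to-treat method: "ITT analysis will use a generalized linear mixed model which can inherently deal with data missing at random".

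Nothing in the section calls the paired tests descriptive, and nothing ranks the three analyses for a given secondary outcome. On the interventions, the article says that "both the groups will be given general dietary and lifestyle advice through the distribution of leaflets".

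**The concern.** A paired test of baseline against week 8 asks whether the members of one arm changed. It does not ask whether the shake changed them more than the usual dinner did. A within-arm change combines any effect of the shake with whatever acts on both arms: the leaflets, being in a trial and repeated measurement, and time. Only the contrast between the randomised arms removes these.

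The plan nevertheless makes the within-arm comparison a formal significance test and writes the threshold beside it. Each continuous secondary outcome will therefore have two within-arm P values as well as between-group results. A report could set a significant shake arm against a non-significant control arm and present that as a benefit. A difference in significance is not a significant difference. At stake are the conclusions on waist, hip, body fat, fat-free mass, blood pressure, lipids, fasting glucose and HbA1c.

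**Working it through.** **Number per arm.** The Sample size section uses an unpooled two-proportion formula with 0.1 and 0.5, two-sided 5%, 80% power and 1:1 allocation:

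(0.1 × 0.9 + 0.5 × 0.5) × ((1.96 + 0.8416) / 0.4)² = 0.34 × 49.06 = 16.68, rounded up to 17.

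Allowing for 20% dropout: 17 / 0.8 = 21.25, rounded up to 22. Both stated figures reproduce. I use 17 as completers per arm and 22 as the case of no dropout.

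**Assumption that the documents do not supply.** Let both arms have the same true mean change d, in units of the SD of the change score, so that the shake adds nothing. The article gives neither an SD nor an expected change for any continuous outcome, so d is varied from 0 to 1.0.

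**Formula.** Let u be the probability that a two-sided 5% paired t-test is significant in the direction of improvement (noncentral t, n − 1 degrees of freedom, noncentrality d√n). Let s be the probability that it is significant in either direction. The arms are independent, so

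P(significant improvement with shake, control not significant) = u × (1 − s).

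For d = 0: 0.025 × (1 − 0.05) = 0.024. For d = 0.2 and n = 17: 0.118 × (1 − 0.118) = 0.104. For d = 0.5 and n = 17: 0.491 × (1 − 0.491) = 0.250.

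| Shared change d | u, n = 17 | Shake-only pattern, n = 17 | Shake-only pattern, n = 22 |
|---|---|---|---|
| 0 | 0.025 | 2.4% | 2.4% |
| 0.2 | 0.118 | 10.4% | 12.3% |
| 0.3 | 0.213 | 16.7% | 19.6% |
| 0.5 | 0.491 | 25.0% | 23.8% |
| 0.7 | 0.773 | 17.5% | 10.6% |
| 1.0 | 0.972 | 2.8% | 0.6% |

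The curve peaks at 25%, where each paired test has about 50% power, and falls on either side.

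**Comparison with the between-group test.** In simulations of 200,000 trials per setting (d = 0, 0.3, 0.5 and 0.7; n = 17 and 22), the two-sample t-test on change rejected in 4.9% to 5.1% of trials whatever the shared change. About half of that, 2.5%, favours the shake. Among trials showing the shake-only pattern at n = 17, the two-sample test was significant in 12.8% (d = 0.3), 9.7% (d = 0.5) and 11.0% (d = 0.7). The planned between-group test would therefore usually not support the story told by the paired tests.

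**The case against.** The strongest reply is that the right test is already in the plan. The sentence after the paired t-tests assigns independent-sample tests to the differences between groups, and the intention-to-treat analysis is a mixed model. A reader might infer from the paired-test sentence that the plan has no randomised comparison for secondary outcomes, or that the shake will be judged by significance in one arm only. The documents support neither reading. It follows that one cannot say the plan's error rate is far above 5%. The percentages above describe a misreading that the text leaves open, not a decision rule that it states.

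The threshold may also be meant as the general level, stated once. The Sample size section separately sets 5% for a between-group contrast. That is a fair reading, but on it the within-arm results are still formal significance tests with no descriptive label.

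The evidence for a shared change is modest. Controls keep their usual dinners, both arms keep their habitual activity, and the main stated common input is a leaflet. Regression to the mean is doubtful for the laboratory measures, since entry selects on BMI and not on them. So the pattern cannot be called frequent without qualification: with no shared change it is no commoner than a chance between-group result in the shake's favour.

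It is also tempting to add that the paired tests use completers only and so conflict with the intention-to-treat rule. That is not specific to them: an independent t-test on change has the same limitation, and the article gives the intention-to-treat role to the mixed model.

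Finally, a separate analysis plan might rank the tests. The point does not rest on that omission. It rests on what the article states: a significance rule written beside tests that do not address the hypothesis.

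**Conclusion.** The point stands in a limited form. The protocol article plans within-arm paired t-tests as significance tests, alongside valid between-group analyses, without saying which decides the secondary outcomes. The paired tests cannot answer the stated secondary hypothesis.

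If their results were read side by side, with no shake effect and 17 completers per arm, a shake-only improvement would appear in about 10% to 25% of trials per outcome at a shared change of 0.2 to 0.5 SD. It would appear in about 2.4% with no shared change and about 3% at 1.0 SD. These rates rest on the assumed shared change, normally distributed change scores and independent arms.

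The primary outcome is outside the problem. The article states: "The primary outcome will be the proportion of participants that had a 5% body weight loss from baseline". That is a binary endpoint, to which a paired t-test does not apply. The sample size is also unaffected. This is a correction that should be made for the secondary outcomes. It does not threaten the trial's main conclusion.

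**What to change.** In the Statistical analysis section:

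1. Report baseline, week-8 value and mean change in each arm descriptively, without P values. If the paired tests are kept, label them as descriptive and as no evidence of a shake effect.
2. State that the 0.05 threshold, with an estimate and 95% confidence interval, applies to the between-group contrast already planned. Name which one decides each continuous secondary outcome: the mixed-model treatment contrast or the between-group comparison of change.

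The cost is a change to one or two sentences. It needs no further data, participants or visits and no change to the sample size. The Trial status section says that enrolment has not begun, so the change can be made before any data exist.

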### Sample size

A sample of 44 healthcare employees who engage in shift work will be recruited for the study after screening for eligibility against the inclusion and exclusion criteria mentioned below. The minimum sample size will be calculated based on the primary outcome, the proportion of participants achieving 5% weight loss after 8 weeks. Previous weight loss intervention trials predicted that 50% of individuals in the intervention group and 10% of participants in the control group would lose at least 5% of their baseline body weight after 8 weeks [23].. To detect this difference in the proportion of participants achieving 5% weight loss between the intervention and control groups, 17 participants were required in each group, to ensure 80% power at a 5% significance level. To accommodate a 20% dropout rate, we, therefore, needed to recruit 22 participants in each intervention group. Hence, a total of 44 adults with obesity (BMI >25 kg/m^2^) will be recruited for the study [24]. The formula used for sample size calculation is presented below:$${n}_B=\left(\frac{P_{\textrm{A}}\left(1-{P}_{\textrm{A}}\right)}{K}+{P}_{\textrm{B}}\left(1-{P}_{\textrm{B}}\right)\right){\left(\frac{Z_{1-\alpha /2}+{Z}_{1-\beta }}{P_{\textrm{A}}-{P}_{\textrm{B}}}\right)}^2$$

*n*
_B_ = Sample size in one arm

*P*
_A_ = Proportion of subjects expected to achieve 5% weight loss at the end of 8 weeks in the placebo group (0.1)

*P*
_B_ = Proportion of subjects expected to achieve 5% weight loss at the end of 8 weeks in the treatment group (0.5)

*Κ* = Sampling ratio (1:1)

*Z*
_α_ = Critical value of the normal distribution at *α* (*α* is 0.05 and the critical value is 1.96)

*Z*
_β_ = Critical value of the normal distribution at *β* (*β* is 0.2)

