### Assignment of intervention

#### Sequence generation

Participants satisfying the eligibility criteria will be allocated to control and intervention groups equally (1:1) using the simple random sampling technique. The randomization assignment will be generated by one independent investigator using a computer-generated random number sequence.

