#### Study schedule

Anthropometric measures, blood pressure, fasting plasma glucose, serum HbA1c, and lipid profile will be measured at the time of recruitment of participants and will be repeated at the end of the 8th week. However, anthropometry measures will be again measured at the end of the 4th week additionally. The details of items that will be measured at every visit are described in Table 1.

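### The continuous secondary outcomes are compared between arms by unadjusted t-tests or rank tests, beside a mixed model whose handling of baseline is not stated; one baseline-adjusted model would use the same data with modestly better precision

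*Protocol article*

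**What the plan says.** All references are to the protocol article.

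- **Between-group test.** Statistical analysis names independent-samples t-tests, "or suitable non-parametric test depending on data distribution) for the between-group differences". The rank test named earlier in that section is the Mann-Whitney test. No baseline covariate is mentioned.
- **Mixed model.** The same sentence adds generalized linear mixed effects models for longitudinal data. The next paragraph makes such a model the intention-to-treat analysis, without limiting it to outcomes with three visits. Its fixed effects and its treatment of baseline are not given. No model is named for the per-protocol set.
- **Outcomes.** Secondary outcomes lists changes in waist, hip, body fat percentage, fat-free mass, blood pressure, lipids, fasting glucose and HbA1c.
- **Timing.** Study schedule says that anthropometry, blood pressure, glucose, HbA1c and lipids "will be measured at the time of recruitment of participants and will be repeated at the end of the 8th week", with anthropometry also at week 4. Table 1 puts body composition at allocation and week 8.
- **Size and allocation.** Sample size states that "17 participants were required in each group, to ensure 80% power at a 5% significance level" and that the trial "needed to recruit 22 participants in each intervention group". Sequence generation says participants will be "allocated to control and intervention groups equally (1:1) using the simple random sampling technique". No stratification on baseline values is described.

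**The concern.** Baseline is usually the strongest single predictor of the week-8 value of the same measure, and the trial collects it for every continuous outcome. A two-sample t-test uses that information imperfectly. Run on week-8 values, it ignores baseline. Run on changes, it subtracts the whole baseline value, which over-corrects unless the correlation is close to 1. In arms of about 20 formed by simple randomisation, noticeable chance differences at baseline are to be expected on some outcomes, and an unadjusted comparison carries part of them into the reported effect.

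At stake are the width of the confidence intervals and the accuracy of the estimates for the secondary metabolic outcomes, given whatever imbalance occurs. There is also an ambiguity: for the same contrast the plan names both a t-test and a mixed model, and does not say which one carries the result.

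**Working it through.** **1. The plan's own sample size.** Inputs from Sample size: "50% of individuals in the intervention group and 10% of participants in the control group", a two-sided test (alpha "is 0.05 and the critical value is 1.96"), 80% power, and "To accommodate a 20% dropout rate".

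n = [0.1×0.9 + 0.5×0.5] × ((1.96 + 0.8416)/0.4)² = 0.34 × 49.06 = 16.68, so 17 per arm; 17/0.8 = 21.25, so 22 per arm. This reproduces the stated figures. They concern the binary primary outcome and do not depend on how the continuous outcomes are analysed.

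**2. Chance imbalance.** The standard error of the baseline mean difference, in SD units, is √(2/n): √(2/17) = 0.34 and √(2/22) = 0.30. The chance of a difference above 0.3 SD in either direction on a given outcome is 38% at 17 per arm and 32% at 22.

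**3. Precision.** The article gives no SD, correlation or target effect for any continuous outcome. Assumptions: equal SDs at baseline and week 8, equal arms, correlation r from 0.5 to 0.9, and a true difference of 0.5 SD. Variance factors are:

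- week-8 values only: 1
- change scores: 2(1 − r)
- baseline-adjusted: 1 − r²

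The ratio of adjusted to change-score variance is (1 − r²)/[2(1 − r)] = (1 + r)/2. The standard error is √(2 × factor/n). Power is from the noncentral t. The adjusted analysis loses one degree of freedom, and its variance is inflated by 1 + 1/(2n − 4), which is 1.033 at n = 17.

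| r | Variance, adjusted ÷ change | Power at 17 per arm: week-8 only | Change | Adjusted |
|---|---|---|---|---|
| 0.5 | 0.75 | 29% | 29% | 36% |
| 0.7 | 0.85 | 29% | 45% | 49% |
| 0.8 | 0.90 | 29% | 61% | 64% |
| 0.9 | 0.95 | 29% | 88% | 89% |

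The variance ratios are before the small-sample inflation; the powers include it. A simulation of 20,000 trials at 17 per arm agrees. Change-score against adjusted standard errors were 0.341 and 0.301 (r = 0.5), 0.217 and 0.209 (r = 0.8), and 0.153 and 0.151 (r = 0.9).

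**4. Where the gain ends.** With the inflation, the ratio at 17 per arm is 1.033(1 + r)/2. It reaches 1 at r = 2/1.033 − 1, about 0.93 to 0.94. Above that there is no gain over change scores.

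**5. Error given an imbalance.** If the arms differ by 0.3 SD at baseline, a week-8 comparison is shifted by 0.3r and a change-score comparison by −0.3(1 − r):

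| r | Week-8 only | Change |
|---|---|---|
| 0.5 | +0.15 SD | −0.15 SD |
| 0.8 | +0.24 SD | −0.06 SD |
| 0.9 | +0.27 SD | −0.03 SD |

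**6. The mixed model.** For an outcome with two visits and complete data, a group-by-time model that leaves the arms' baseline means free returns the difference in mean change, which is the change-score estimate. It gains the adjusted precision only if baseline is a covariate or the baseline means are constrained equal across arms.

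**The case against.** The strongest reply is that the t-test is not the whole plan. The intention-to-treat analysis is a mixed model, a baseline and a week-8 value are already repeated measures, and the handling of baseline may be set out in an analysis plan that is not shown. This stands in part. It would be wrong to infer that unadjusted t-tests are the only between-group analysis. The silence about baseline in the mixed model is also not itself a fault in an article. It does not settle the matter, though: the article does fix the t-test for between-group differences, and one common form of the mixed model gives the change-score estimate (step 6).

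Second, the outcomes are defined as changes. That also stands. A reader might take the 29% row and conclude that adjustment more than doubles power, from 29% to 64% at r = 0.8. This needs a comparison of week-8 values alone. The Statistical analysis section does not exclude that, but the Secondary outcomes section points the other way.

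Third, randomisation protects the t-test. A reader might infer bias or an inflated type I error; neither follows. The estimate is unbiased over repeated randomisation and the test is valid. The cost is lost precision, and error conditional on the imbalance actually seen.

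Fourth, only secondary outcomes are involved. Nothing here bears on the responder outcome or on the 44 participants.

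**Conclusion.** The point holds as a worthwhile improvement to a stated method for the continuous secondary outcomes. Against change-score t-tests, baseline adjustment lowers the variance by about 25% at r = 0.5, 15% at 0.7, 10% at 0.8 and 5% at 0.9. At 17 per arm, power for a 0.5 SD effect rises by about 7, 4 to 5, 3 and less than 1 percentage points. The gain is larger only if week-8 values are compared without baseline. Adjustment also removes the conditional error from chance imbalance, which on change scores is up to 0.15 SD for a 0.3 SD imbalance at r = 0.5.

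These sizes rest on assumed correlations, equal SDs and an assumed 0.5 SD effect, because the article gives none of them. The direction does not depend on the exact values until r exceeds about 0.93.

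**What to change.** In Statistical analysis, name one baseline-adjusted model as the between-group analysis for each continuous outcome, in both the intention-to-treat and per-protocol sets. Either of these would do:

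- a linear model for the week-8 value on randomised arm and the baseline value of the same outcome; or
- the planned mixed model with baseline as a covariate, or with baseline means constrained equal across arms, taking the week-8 arm contrast. This suits waist and hip, which also have week-4 values.

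Report the adjusted mean difference with a 95% confidence interval. Log-transform skewed outcomes such as triglycerides where needed, so that the provision for asymmetrical data is kept. State that the t-tests and Mann-Whitney tests are descriptive or sensitivity analyses, so that one method carries each result.

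The cost is a few sentences and one degree of freedom per outcome. No new data are needed, and Trial status says enrolment had not begun. The downside is little or no gain over change scores for outcomes with a correlation above about 0.93.
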